##### Low and moderate dose intervention groups

The low and moderate dose intervention groups will be asked to follow a 12-week online yoga prescription (for 60 and 150 min/week, respectively). We selected the low dose of 60 min/week because this is the minimal amount needed to experience mental and/or physical health benefits [40, 52–55]. We chose the moderate dose of 150 min/week because this reflects the physical activity guidelines [56].

The style of the online yoga videos will be Hatha because (1) Hatha combines a physical practice with a meditative component to cultivate mindfulness (i.e., moment to moment, non-judgmental awareness, cultivated by paying attention in a specific way) [57] and self-awareness and (2) includes instruction from a variety of lineages (e.g., Iyengar, Asthanga, Vinyasa). The online prescription assures the poses used are identical for both intervention groups. Participants will be asked to complete the yoga videos in a specific order, which will include specialized preparatory instructions for each video to ensure comfort and safety [56].

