The study will be stopped prior to its completion based upon (1) clinical deterioration of PTSD symptomology (increased scores of >20 points from baseline on the Impact of Event Scale-Revised (IES-R) in >50% of the enrolled participants), (2) difficulty in study recruitment (i.e., at halfway through the timeline of recruitment, study recruitment falls below 30% of the total recruitment goal), and (3) if any new safety information or research becomes available during the trial that necessitates stopping.

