### Allocation (phase 2 only)

Block randomization will be used to assign participants to treatment groups. Specifically, the biostatistician will construct 15 blocks of six participants using SAS PROC PLAN with a random number seed known only by the biostatistician. This will be done at the beginning of the study (front-loaded) and provided to a research staff member not associated with this study (i.e., trusted broker). The trusted broker will utilize the treatment allocations to sequentially assign enrollees to randomized treatment groups (the biostatistician will be shielded from enrollment date and enrollment order, and participant IDs will not reflect enrollment order). The trusted broker will hold the codes that match participants to treatment groups. Research staff members will call the trusted broker to determine assignment to group. In case of adverse events (AE), the research staff member will call the trusted broker to provide for unblinding (AE only). After randomization, participants will be emailed a study information packet (i.e., instructions, UDAYA username/password) according to the intervention assigned. The initiation of the study will begin after allocation to study arm (see Fig. 2 for phase 2 study flow chart).

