### Blinding (phase 2 only)

The principal investigator and biostatistician will remain blinded until the completion of data collection (i.e., data is locked). Following the conclusion of data collection (i.e., data is locked), the biostatistician will be unblinded as data analysis will require knowledge of treatment assignment. The study coordinator and graduate student worker that deliver the intervention(s) and prepare reports to the Independent Monitoring Committee (IMC) will be unblinded. The study coordinator will be responsible for the intervention groups, and the graduate student worker will be responsible for the control group. A research staff not directly involved in the study will serve as the “trusted broker” to handle the sequential assignment of participants to randomized treatment groups and will also be unblinded.

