#### Adverse events

An AE is any untoward medical occurrence in a subject during participation in the clinical study or with use of the experimental agent being studied. An adverse finding can include a sign, symptom, abnormal assessment (laboratory test value, vital signs, electrocardiogram finding, etc.) or any combination of these regardless of relationship to participation in the study. Adverse events that are non-serious will be provided to the IMC with summaries of the numbers and rates of AEs by group.

Expedited review will occur for all events meeting the FDA definition of serious adverse events (SAEs), i.e., any fatal event, immediately life-threatening event, and permanently or substantially disabling event. This also includes any event that a study investigator or the IMC judges to impose a significant hazard, contraindication, side effect, or precaution. For purposes of this study, all SAEs will be reported to the IMC regardless of any judgment of their relatedness to the study treatment.

The PI will record all reportable events with start dates occurring any time after informed consent is obtained until 7 (for non-serious AEs) or 30 days (for SAEs) after the last day of study participation. Each week, participants will report in their weekly logs the occurrence of AE/SAEs since the last week. If the participants are not completing their logs, they will be prompted via email by the research team to complete their logs. If there are two consecutive failed email attempts, the participants will be called. Events will be followed for outcome information until resolution or stabilization.

The research team will determine if the event is an AE or an SAE. If an SAE, the research team will complete a form to be provided to the IMC to meet and investigate the SAE until determined resolved or stable and its relation to the study (related or not related). Once recruitment begins, IMC will meet twice a year and will meet ad hoc when AE or an SAE occur. AE reports and annual summaries will not include individual identifiable private information about the human subjects. Each report will only include the identification code previously assigned.

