At 6 weeks (midway through the intervention), participants will be asked to complete the IES-R and answer a 1-item Likert-based question related to whether they think the intervention is contributing to their symptoms for the IMC to review. Every 2 weeks of the intervention, participants will be asked to fill out the PHQ-9 via Qualtrics within 48 h. A research team member will monitor PHQ-9 completion daily (including weekend/holidays). Women with scores suggestive of clinical depression (>15) will be notified and advised to follow up with their primary care physician. If suicidal ideation is noted with a screen score of two or three on question 9 of the PHQ-9, the participant will be contacted within 24 h by a crisis-trained, clinical staff for further assessment of risk. Clinical providers trained by the MISS Foundation are well equipped to handle psychological crises, have a system currently used for their existing 3000 grieving families they help annually, and have staff available on weekends/holidays. If imminent suicidal risk is present, the staff will follow MISS Foundation emergency procedures to ensure participant safety, and the participant will be discontinued from the study. If there are no concerns for active suicidal risk after the phone assessment, the participant will be able to continue in the study if she desires. All participants will have the MISS Foundation provider’s phone number, and the research personnel can either email, call, text, or page the lead clinical provider to respond to psychiatric issues. Depending on the need of the participant, one of them will be able to talk to a clinician within 2 to 3 h.

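### The one numeric harm stopping rule pools three arms of 30, so it can scarcely detect harm in a single arm, and the protocol contradicts itself on whether the IMC sees safety data by arm

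*Protocol article*

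**What the plan says.** The Procedures section (Phase 2) gives three grounds for stopping the study early. The first is clinical deterioration of PTSD symptoms, defined as "increased scores of >20 points from baseline on the Impact of Event Scale-Revised (IES-R) in >50% of the enrolled participants". The second is slow recruitment. The third has no number: "if any new safety information or research becomes available during the trial that necessitates stopping". Only the first is a numeric rule about harm, and its count and denominator run over all three arms.

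The Adverse events section says that non-serious adverse events (AEs) reach the IMC with "summaries of the numbers and rates of AEs by group". It also says that the "IMC will meet twice a year and will meet ad hoc when AE or an SAE occur", and that at week 6 "participants will be asked to complete the IES-R and answer a 1-item Likert-based question" on whether the intervention contributes to symptoms, for the IMC to review. No threshold or split by arm is given for that review.

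The Reporting section describes the study reports made for the IMC. It lists adverse events and stopping rules among their contents, then says the tables will come only from aggregate baseline and safety data, not split by assignment.

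On who prepares the reports, the Blinding section says: "The study coordinator and graduate student worker that deliver the intervention(s) and prepare reports to the Independent Monitoring Committee (IMC) will be unblinded". The principal investigator and the biostatistician stay blinded until data lock.

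**The concern.** The women enter with clinical-level PTSD symptoms (IES-R of 33 or more, Table 2). The trial compares two doses of the same practice: "The online prescription assures the poses used are identical for both intervention groups". Harm in one yoga arm alone would therefore point to dose, which is a contrast the trial is built to study. A pooled rule dilutes such a signal with the two unaffected arms.

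A pooled rule is tolerable if the IMC sees data by arm and can use judgement. If the Reporting section governs, the periodic tables would not show an arm-level shift in IES-R or PHQ-9. The two weaknesses then reinforce each other.

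**Working it through.** **Inputs.** Enrolment of 90 (Sample size), with 20% attrition leaving 90 × 0.80 = 72. Allocation in 15 blocks of six (Allocation): 15 × 6 = 90, so 30 per arm. Threshold of more than 50% of enrolled women (Procedures). The protocol states no count for the rule and no expected rate of worsening, so every rate below is an assumption, shown over a range.

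**Count needed at full enrolment.**
- More than 50% of 90: at least 46 women.
- Largest contribution from one arm: 30/90 = 33.3%.
- Still needed from the other two arms: 46 − 30 = 16 of 60 = 26.7%.
- Harm confined to both yoga arms: 46/60 = 76.7% of them must worsen.

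**Effect of attrition.** Take 24 observed per arm (equal loss assumed).
- If the 72 observed women are the denominator, 37 are needed: 37 − 24 = 13 of 48 = 27.1% from the other arms.
- If the denominator stays at 90 enrolled and lost women count as not worsened: 46 − 24 = 22 of 48 = 45.8%. For both yoga arms: 46/48 = 95.8%.

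**Chance that the pooled rule is met.** P(X₁ + X₂ + X₃ ≥ 46), each Xᵢ binomial with n = 30, by exact convolution.

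| Harmed arm(s), true rate | Other arm(s) 10% | Other arm(s) 20% |
|---|---|---|
| One arm, 50% | 1.0e-10 | 8.6e-6 |
| One arm, 70% | 1.0e-7 | 0.0010 |
| One arm, 100% | 0.0002 | 0.13 |
| Both yoga arms, 50% | 0.002 | 0.017 |
| Both yoga arms, 60% | 0.06 | 0.21 |
| Both yoga arms, 70% | 0.45 | 0.73 |

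**The same >50% criterion within one arm, single look.** P(at least 16 of 30) and P(at least 6 of 10).

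| True rate in that arm | 30 assessed | 10 assessed |
|---|---|---|
| 30% | 0.006 | 0.05 |
| 40% | 0.10 | 0.17 |
| 50% | 0.43 | 0.38 |
| 60% | 0.82 | 0.63 |
| 70% | 0.98 | 0.85 |

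**False prompts.** Let q = P(at least 6 of 10) at a background rate common to all arms. The chance of a prompt in at least one of three arms is 1 − (1 − q)³.
- 10% background: q = 0.00015, giving 0.04%.
- 20%: q = 0.0064, giving 1.9%.
- 30%: q = 0.0473, giving 13.5%.

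Checking after every woman from 10 to 30 per arm raises these to about 0.1%, 4% and 30%.

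**The two reporting statements side by side.** The Adverse events section gives the IMC AE numbers and rates by group. The Reporting section covers IMC reports that include adverse events and restricts their tables to aggregate data. Because it says only, and because AEs are among the listed contents, staff preparing those reports cannot follow both.

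**The case against.** The strongest reply is that the rule does what it claims. It defines when the whole study stops, and a denominator of all enrolled women is coherent for that purpose. That stands, and the rule should be kept.

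The second reply is that detection does not rest on this rule. The AE definition is broad enough that marked symptom worsening might be recorded as an AE. Any event that an investigator or the IMC judges a significant hazard gets expedited review. The IMC meets ad hoc for AEs and reviews the week-6 IES-R, the third criterion allows stopping on new safety information, and the trusted broker can unblind an individual case after an AE. PHQ-9 every two weeks, with crisis contact, protects each woman. This also stands: a reader might infer that participants are unprotected or that harm in one arm could never stop the trial, and the protocol supports neither. These routes work by case or by judgement, however. None sets an arm-level limit for worsening, and judgement about an arm needs data by arm.

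The third reply is that the two reporting statements cover different things, separate AE summaries and periodic tables. That would be workable, but the text does not say it. A reader might equally infer that the IMC never sees arm-level data; that goes too far, since the Adverse events section says otherwise for non-serious AEs. What the document shows is a conflict.

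Finally, the separate data and safety monitoring plan, mentioned as approved under Research ethics approval, is not shown and may hold more detail. The point here rests on the denominator and table format that the article itself fixes, and does not rely on detail being absent.

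**Conclusion.** The point holds as a design weakness that should be fixed. At full enrolment the only numeric harm rule needs 46 of 90 women, so even an arm in which all 30 worsen needs 16 of the other 60. That count is exact. Under assumed worsening of 10% to 20% elsewhere, the chance of meeting the rule with 70% harmed in one arm is 0.001 or less, and with every woman in one arm harmed it is 0.0002 to 0.13. The probabilities assume independent women, full assessment of 90 and the stated rates. Keeping 90 as the denominator under attrition makes the rule harder to meet.

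Separately, the Adverse events and Reporting sections cannot both be followed. The consequence for arm-level IES-R and PHQ-9 trends is conditional: they would be hidden in the periodic tables if the Reporting section is applied. Individual safeguards and IMC discretion keep this below a critical defect.

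**What to change.** Amend the Reporting section so that the IMC receives closed safety tables by coded arm, covering AEs, week-6 IES-R and PHQ-9. The staff who already prepare IMC reports are unblinded and can produce them, and the principal investigator and biostatistician remain blinded. Having the trusted broker prepare the tables, to separate this from intervention delivery, is optional.

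Keep the pooled rule as the whole-study halt. At the scheduled IMC reviews, once about 10 women per arm have been assessed, apply the same >50% criterion within each arm as a prompt for IMC review, not as an automatic stop. State that the IMC should still judge signals below that level.

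The cost is a protocol amendment, which goes to the IMC, then NCCIH, then the IRB, and a split of existing tables. Numbers per arm are small. Sensitivity is limited: about 0.4 at a true 50% rate and 0.85 to 0.98 at 70%. If the background rate of worsening is near 30%, false prompts become common enough (13.5% at one look) that the criterion should stay tied to scheduled reviews and should not be checked after each woman.

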### Outcome measures

#### Phase 2

Table 3 outlines the outcome measures and associated time points.

**Table 3 Tab3:** Summary of data collection

	Baseline	12 weeks	20 weeks
Demographics	X		
Feasibility (acceptability, demand, practicality)			
Interviews		X	X
Acceptability			
Satisfaction survey		X	
Demand			
Udaya.com tracking system	X	X	
Daily log	Daily		
Practicality			
Udaya.com tracking system	X	X	
Satisfaction survey		X	
PTSD symptoms			
Impact of Event Scale-Revised	X	X	X
Comorbid conditions			
State-Trait Anxiety Inventory (anxiety)	X	X	X
PHQ-9 Patient Health Questionnaire (depression)	X	X	X
Self-compassion			
Self-Compassion Scale	X	X	X
Emotional regulation			
Emotional Regulation Questionnaire	X	X	X
Grief			
Perinatal Grief Scale	X	X	X
Sleep quality			
GENEActiv	X	X	X
Pittsburgh Sleep Quality Index	X	X	X
Physical activity			
GENEActiv	X	X	X
Past-week Modifiable Activity Questionnaire	Weekly		
Daily log			
Yoga sessions	Daily		
Borg Rating of Perceived Exertion Scale	Daily		
Meditative Movement Inventory	Daily		
Self-rated health			
Short-Form 12 Health Survey	X	X	

##### Feasibility (acceptability, demand, and practicality)

We will utilize Bowen and colleagues’ [60] standards for feasibility studies. *Acceptability* measures include satisfaction with the online-streamed yoga intervention, perceived appropriateness of the intervention for this population, and intent to continue using intervention materials and will be assessed via satisfaction survey at post-intervention. *Demand*, including expressed interest in participating in study and actual use of intervention, will be measured via Udaya.com online tracking (i.e., # times logged in, time spent in class, completion of class, date/time of class access) and daily logs (i.e., yoga sessions, Borg Rating of Perceived Exertion Scale, and Meditative Movement Inventory). *Practicality* measures, including the ability of participants to carry out intervention activities (i.e., yoga), will be assessed via the Udaya.com tracking system, weekly logs, and satisfaction survey at the end of the intervention. *Qualitative interviews* following best practices for conducting interviews, including developing a priori questions and written moderator protocol and recording and transcribing data [61, 62], will be used to supplement information gained from the satisfaction surveys and to further understand the use of non-pharmacological interventions such as yoga in this population. Qualitative interviews will be administered in the intervention groups at post-intervention (12 weeks) and at follow-up (20 weeks).

For the intervention group(s), our benchmarks will be as follows: (1) feasibility (i.e., satisfaction, useful, appropriate, acceptable ≥70%, (2) demand (i.e., recommend to others, continue to use skills, program easy to complete ≥70%, and (3) attendance (i.e., at least 70% of participants in the moderate dose group will complete 150 min of yoga/week for at least nine of the 12 weeks (75%), at least 70% of participants in the low dose group will complete 60 min of yoga/week) for at least nine of the 12 weeks (75%). For the control group, our benchmarks will be as follows: (1) feasibility (i.e., satisfaction, appropriate, acceptable ≥70%) and (2) attendance (i.e., at least 70% of the control group will complete 60 min of stretching, toning, and limbering/week for at least nine of the 12 weeks (75%).

##### PTSD symptoms

The IES-R has three subscales (i.e., avoidance, intrusion, hyperarousal), and the sum of the three subscale scores produce the total IES-R score. All subscale scores have demonstrated high internal consistency and have been validated in postpartum populations [63]. A total IES-R score is clinically significant, and ≥33 signifies the likely presence of PTSD [64].

##### Anxiety

The State-Trait Anxiety Inventory (STAI) yields scores indicating levels of trait (Form Y-1) and state anxiety (Form Y-2). The STAI has demonstrated reliability and validity in pregnant and postpartum populations [65, 66]. Higher scores indicate greater anxiety.

##### Depression

The Patient Health Questionnaire-9 (PHQ-9) [67] is a valid and reliable (*α* = 0.86–0.89) measure used to screen, diagnose, monitor, and measure the severity of depression and has been validated in pregnant and postpartum populations [68–70]. Scores range from 0–27, and cut-off scores of 5, 10, 15, and 20 represent mild, moderate, moderately severe, and severely depressive symptoms, respectively.

##### Self-compassion

The Self-Compassion Scale (SCS) is a 26-item questionnaire with good construct validity and reliability (*α* = 0.92) [71]. Higher scores indicate higher levels of self-compassion.

##### Emotional regulation

The Emotional Regulation Questionnaire (ERQ) is a valid 10-item scale used to measure an individual’s tendency to regulate their emotions by two strategies (i.e., cognitive reappraisal and expressive suppression) [72]. The higher the scores, the greater the use of the emotional regulation strategy.

##### Mindfulness

The Mindful Attention Awareness Scale (MAAS) is a valid and reliable measure with good internal consistency (*α* = 0.80–0.87) [73]. This scale includes 15 items and measures the extent to which individuals are able to maintain awareness of present-moment experience. Higher scores reflect higher levels of mindfulness.

##### Grief

The Perinatal Grief Scale (PGS) is a valid 33-item instrument used to quantify the grief of perinatal loss [74]. The PGS consists of three subscales (i.e., active grief, difficulty coping, and despair). Higher scores indicate more intense grief.

##### Self-rated health

The Short-Form Health Survey (SF-12) was developed for the Medical Outcomes Study (MOS) and is modified from the original 36-item survey [75]. The SF-12 is a valid scale that includes 12 items that measure eight domains of health-related quality of life (i.e., physical functioning, role physical, bodily pain, general health, vitality, social functioning, role emotional, and mental health). The items are scored using standard scoring algorithms explained elsewhere [76]. Scores range from 0 (lowest level of health) to 100 (highest level of health).

##### Subjectively measured sleep quality

The Pittsburgh Sleep Quality Index (PSQI) is a 19-item questionnaire [77]. The PSQI has demonstrated reliability and validity in pregnant populations [78]. Higher global PSQI scores indicate more sleep disturbances.

Subjectively measured physical activity: The past-week Modifiable Activity Questionnaire (PWMAQ) is a valid and reliable self-report measure (*α* = 0.82) [79]. Respondents report the number of minutes spent in 38 different activities, and each activity is summed. Using the Compendium of Physical Activities, a MET value of >3.0 will be applied to each reported activity (at least a moderate-intensity). Participants will be categorized as meeting physical activity guidelines if they reported at least 150 min of moderate-intensity physical activity during the past week.

##### Objectively measured sleep quality and physical activity

The GENEActiv (ActivInsights, Kimbolton, UK) accelerometer will be used to provide an objective, non-invasive 24-h Assessment of Sleep-Wake and Physical Activity patterns. Wrist actigraphy has been extensively validated as a measure of sleep-wake activity as compared to the gold standard sleep measure, polysomnography, in samples from infants to older adults [80–82]. The GENEActiv also has been validated for sedentary behavior and postural allocation (i.e., sitting vs. standing), and moderate to vigorous physical activity [83, 84]. Bed times and wake times (to define the sleep interval) will be derived from brief daily diaries which can be completed in less than 1 min.

